## Abstract

**Introduction:**

Post-induction hypotension (PIH) is a common event in elderly surgical patients and is associated with increased postoperative morbidity and mortality. This study aims to develop and validate a PIH prediction model for elderly patients undergoing elective non-cardiac surgery to identify potential PIH in advance and help to take preventive measures.

**Methods and analysis:**

A total of 938 elderly surgical patients (n=657 for development and internal validation, n=281 for temporal validation) will be continuously recruited at The First Affiliated Hospital of Soochow University in Suzhou, China. The main outcome is PIH during the first 15 min after anaesthesia induction or before skin incision (whichever occurs first). We select candidate predictors based on published literature, professional knowledge and clinical expertise. For model development, we will use the least absolute shrinkage and selection operator regression analysis and multivariable logistic regression. For internal validation, we will apply the bootstrapping technique. After model development and internal validation, temporal validation will be conducted in patients recruited in another time period. We will use the discrimination, calibration and max-rescaled Brier score in the temporal validation cohort. Furthermore, the clinical utility of the prediction model will be assessed using the decision curve analysis, and the results will be presented in a nomogram and a web-based risk calculator.

**Ethics and dissemination:**

Ethical approval was obtained from the Ethics Committee of the First Affiliated Hospital of Soochow University (Approval No. 2023-012). This PIH risk prediction model will be published in a peer-reviewed journal.

**Trial registration number:**

ChiCTR2200066201.

Strengths and limitations of this studyThis is a prospective cohort study to develop and validate a post-induction hypotension (PIH) prediction model for elderly patients undergoing non-cardiac surgery.The candidate predictors are selected based on the most recent published literature and clinical expertise, with easy availability and convenient clinical application.This study includes the development, internal and temporal validation of the PIH prediction model.The study is limited to anaesthesia induction period, without postoperative outcomes such as complications and mortality.This is a single-centre study, and multicentre cohort studies are warranted for further external validation.

## Introduction

Hypotension is common among patients undergoing surgery and general anaesthesia. It is closely correlated with adverse perioperative outcomes, such as myocardial injury, myocardial infarction, acute kidney injury and death.^1 2^ Accumulating evidence suggested that even short-term hypotension is hazardous to patients during non-cardiac surgery.^3 4^ Approximately 50% of hypotension events occur between anaesthesia induction and surgical incision,^5 6^ which is called post-induction hypotension (PIH). Elderly patients are often frail with comorbidities and low physiological reserve, making them more prone to perioperative hypotension. Compared with intraoperative hypotension related to multiple factors, PIH is mainly attributable to patients’ preoperative conditions and anaesthetic medications, which can be predictable and preventable.

Advanced age, baseline blood pressure, preoperative comorbidities, and type and dose of anaesthetics are associated with PIH.^7 8^ Preoperative volume status and sympathetic activity are also involved in PIH.^9 10^ With further investigation, some PIH prediction models have been developed; however, they are mostly derived from retrospective studies with missing data and limited number of factors, and some studies included patients in a single type of surgery only.^11–14^ In recent years, new predictors have been reported, such as inferior vena cava-related parameters^15–17^ and perfusion index.^18^ Nonetheless, requiring specific equipment or techniques makes those predictors often difficult to be applied in the clinical practice.

Therefore, we designed this prospective cohort study to develop a universal and convenient PIH prediction model for elderly patients undergoing elective non-cardiac surgery. Using this model, we can identify potential hypotension events in advance and take preventive measures to improve anaesthesia management and patient outcomes.

## Methods

### Study design

This single-centre prospective cohort study was conducted at the First Affiliated Hospital of Soochow University between December 2022 and August 2023. The protocol and results of this study will be reported following the transparent reporting of a multivariable prediction model for individual prognosis or diagnosis (TRIPOD) checklist (online supplemental file 1).^19^

10.1136/bmjopen-2023-074181.supp1Supplementary data

### Study population

#### Inclusion criteria

Aged 65 or greater and both genders.American Society of Anaesthesiologists (ASA) physical status classification I−III.Undergoing elective non-cardiac surgery under general anaesthesia with tracheal intubation.The duration of the surgery is longer than 30 min.

#### Exclusion criteria

Patients who have severe cardiovascular and cerebrovascular diseases, severe liver, kidney or lung dysfunction.Undergoing nerve blocks, spinal or epidural anaesthesia.Pre-existing tracheal intubation, tracheotomy or ≥2 attempts of intubations.Refusal for participation.

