### Study outcome

The study outcome is PIH during the first 15 min after anaesthesia induction or before skin incision (whichever occurs first). Preoperative baseline blood pressure will be recorded when patients are comfortably seated in the ward. During anaesthesia induction, patients will be monitored using non-invasive cuff blood pressure at 1 min interval. Hypotension is defined as either a 30% reduction in mean arterial pressure (MAP) from baseline or absolute MAP ≤65 mm Hg. Dual definitions for diagnosis of hypotension (either a relative reduction in MAP or an absolute threshold of MAP) have been used in many recent studies.^20–25^

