### Data collection

#### Study plan

One day before surgery, a research assistant will identify eligible patients and inform them about the procedures and study aims. During the study, patients can withdraw their consent at any time. If the surgery is cancelled or the exclusion criteria are met, the patient will be excluded. Figure 1 shows the study flowchart.

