#### Intraoperative potential predictors

A total of eight intraoperative potential predictors:

Vital signs including MAP and HR immediately before anaesthesia induction.Dose of anaesthetics used for induction, including propofol, etomidate, ciprofol, esketamine, fentanyl and sufentanil.

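### Excluding patients with two or more intubation attempts selects on a fact known only after induction, so the model is built and validated in a group that cannot be recognised when it is used

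*Protocol article*

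**What the plan says.** The Exclusion criteria contain the line "Pre-existing tracheal intubation, tracheotomy or ≥2 attempts of intubations". Eligibility is screened on the day before the operation: "One day before surgery, a research assistant will identify eligible patients and inform them about the procedures and study aims". The same Study plan section then adds: "If the surgery is cancelled or the exclusion criteria are met, the patient will be excluded".

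The Study outcome section fixes the window: "The study outcome is PIH during the first 15 min after anaesthesia induction or before skin incision (whichever occurs first"). Blood pressure is read every minute by cuff during induction.

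The purpose is given in the Abstract, "to identify potential PIH in advance and help to take preventive measures", and again in the Introduction: "Using this model, we can identify potential hypotension events in advance and take preventive measures to improve anaesthesia management and patient outcomes". The latest candidate predictors, under Intraoperative potential predictors, are "Vital signs including MAP and HR immediately before anaesthesia induction" and the doses of the induction drugs.

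The Inclusion criteria also state: "The duration of the surgery is longer than 30 min". They do not say whether planned or observed duration is meant.

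**The concern.** The population for a prediction model should be recognisable at the moment the model is applied. The first two items in the exclusion line, an existing tube or a tracheotomy, meet that test because they can be seen at screening. The third does not. A second attempt can happen only once the patient has been induced, by which time the outcome is already being measured.

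Whoever opens the nomogram or web calculator before induction cannot know whether this patient will need one attempt or two, and so cannot know whether the predicted risk applies. The removal may also be related to the outcome, since repeated laryngoscopy, or extra drug given with it, could plausibly change blood pressure in the same window. That is clinical reasoning; the protocol gives no figure for it. At stake is whether the reported discrimination, calibration and decision-curve results describe the patients in whom the tool is to be used.

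**Working it through.** **Timing, set side by side**

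1. Day before surgery: eligibility screened and preoperative predictors recorded (Study plan).
2. Immediately before induction: MAP and HR recorded (Intraoperative potential predictors).
3. Induction: drug doses become known, and the outcome window opens (Study outcome).
4. Intubation: the number of attempts becomes known. All patients are intubated (Inclusion criteria), and intubation precedes skin incision, so incision cannot close the window before the attempts are counted. Only the 15-minute limit could.
5. Window closes at 15 min or at incision.

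The exclusion is decided at step 4. Every candidate predictor is available by step 3, and preventive use requires a prediction no later than that. The selection therefore uses information later than any predictor.

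**Validation**

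One set of eligibility criteria is given, with no separate set for the temporal cohort. The 657 and the 281 are thus selected alike, and agreement between them says nothing about patients who needed a second attempt.

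**The plan's own figure**

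Inputs from Sample size estimation: 23 candidate predictors, 10 events per variable, incidence 0.35.

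- 23 × 10 / 0.35 = 657.1, which reproduces the stated 657.
- Expected events in development: 657 × 0.35 = 230. In temporal validation: 281 × 0.35 = 98.

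The point does not alter this calculation.

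**Size, by assumption only**

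The protocol gives neither the fraction f with repeat attempts nor their PIH risk p. Taking 35% as the risk in those retained, incidence among all patients identifiable before induction is (1 − f) × 0.35 + f × p.

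| f (assumed) | p = 20% | p = 50% |
|---|---|---|
| 2% | 34.7% | 35.3% |
| 5% | 34.25% | 35.75% |
| 10% | 33.5% | 36.5% |
| 15% | 32.75% | 37.25% |

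For scale, the standard error of a 35% incidence in 657 patients is √(0.35 × 0.65 / 657) = 0.0186, or about 1.9 points. Only the most extreme row (2.25 points either way) exceeds one standard error. The effect on coefficients, AUC or calibration cannot be calculated from what the protocol gives.

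**The case against.** The best defence is that the restriction is deliberate. The Introduction attributes PIH mainly to the patient's preoperative state and the anaesthetic drugs, and leaving out repeated laryngoscopy isolates that. The model would still be valid for uncomplicated intubations. Induction dose is a candidate predictor, so part of any difference in risk may be captured anyway, and the average effect is probably small.

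What stands is that the effect on overall incidence is likely to be small and that the model is not invalid for patients intubated at the first attempt. What does not stand is the rationale. Isolating a cause suits an aetiological question, whereas a predictive tool needs a population known at the time of use. Whether dose absorbs the difference cannot be checked if these patients are never in the data.

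Three stronger readings are tempting, and the protocol does not support them:

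- *A reader might infer that patients whose operation turned out to last 30 min or less are also dropped afterwards.* The duration rule is an inclusion criterion, screening takes place the day before, when only a planned duration exists, and the exclusion list has no duration item for the later removal rule to act on. This is an ambiguity of wording.
- *A reader might infer that events per variable fall below 10.* With f of 2% to 15%, 657 × (1 − f) × 0.35 / 23 would be 9.8 to 8.5, but only if the 657 are counted before exclusion and not replaced. The protocol does not say so. The model-development and validation sections treat 657 as the cohort analysed, and recruiting until that number is reached fits the text at least as well.
- *A reader might infer that risk in the excluded patients is mis-stated by some definite amount, such as 15 to 20 points.* Any such figure only restates an assumed difference.

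Feasibility is a fair caution. The Study design section describes conduct from December 2022 to August 2023 in the past tense, and the protocol does not say that readings are kept for patients removed after induction.

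**Conclusion.** The point holds for the clause on two or more intubation attempts. That clause conditions the study group on an event after induction, normally inside the outcome window, and this conflicts with the stated aim of advance identification. Temporal validation shares the selection and cannot expose it.

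The consequence is chiefly a mismatch between the group studied and the group in which the model will be used. Its size is unknown because the protocol gives neither the rate of repeat attempts nor the PIH risk in those patients. Under the assumed ranges above, the shift in overall incidence is 0.3 to 2.25 points at the extremes of risk and zero if the risks are equal. The conclusion rests on two readings: that the clause refers to the study anaesthetic, and that the removal rule in the Study plan section applies to it as written. The 657 stands, and the 30-minute criterion is not an error in itself.

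**What to change.** - Define the main analysis population in both cohorts by facts known before induction, and drop two or more attempts as an exclusion from that analysis. Keep these patients wherever their readings exist.
- Report how many patients were removed after induction, by cohort and reason.
- Give a sensitivity analysis without patients who had two or more attempts.
- If recruitment is over and their readings were not kept, state as a limit on applicability that the predicted risks refer to patients intubated at the first attempt, which cannot be known when the model is used.
- Clarify that the 30-minute criterion means planned duration.

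The cost is low. Pressure is already read every minute during induction, so no new measurement is needed. If recruitment has closed, the change is one of analysis, limited to the data retained. The outcome may be slightly noisier and the AUC slightly lower, but it would then describe the patients in whom the tool is to be used.

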### Study outcome

The study outcome is PIH during the first 15 min after anaesthesia induction or before skin incision (whichever occurs first). Preoperative baseline blood pressure will be recorded when patients are comfortably seated in the ward. During anaesthesia induction, patients will be monitored using non-invasive cuff blood pressure at 1 min interval. Hypotension is defined as either a 30% reduction in mean arterial pressure (MAP) from baseline or absolute MAP ≤65 mm Hg. Dual definitions for diagnosis of hypotension (either a relative reduction in MAP or an absolute threshold of MAP) have been used in many recent studies.^20–25^

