**Figure 1 F1:**
[figure not shown]
Study flowchart.

Candidate predictors are selected based on published data,^14^ professional knowledge and clinical expertise. The following clinical variables will be recorded in the case report forms (online supplemental file 2). The research assistant will fill out the preoperative potential predictors section of the form during the preoperative visit, and document variables in the intraoperative potential predictors section and values of heart rate (HR) and non-invasive cuff blood pressure (NIBP) in the outcome section during the case when looking at the monitor.

10.1136/bmjopen-2023-074181.supp2Supplementary data

During the analysis phase, we will calculate MAP at each time point using the traditional formula (MAP=diastolic blood pressure+0.33×pulse pressure), and we will calculate the relative threshold (30% MAP reduction from baseline). Based on these, we can determine the occurrence of PIH.

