#### Preoperative potential predictors

A total of 15 preoperative potential predictors:

Demographic data including age, gender and body mass index.ASA physical status.Comorbidities including hypertension, diabetes mellitus and the age-adjusted Charlson Comorbidity Index score.Autonomic nervous system function (assessed by symptoms and anamneses).^26 27^Myocardial injury (assessed by anamneses and preoperative examinations).Vital signs in the surgical ward including MAP and HR.Preoperative anxiety assessed by the first four items of the Amsterdam Preoperative Anxiety and Information Scale (APAIS).^28^Preoperative frailty evaluated with the FRAIL (fatigue, resistance, ambulation, illnesses, and loss of weight) scale.^29 30^Preoperative volume of fluid infusion and fasting duration.

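### Patients who already meet the hypotension definition just before induction are not set apart, so hypotension that persists from before anaesthesia will almost always be counted as post-induction hypotension

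*Protocol article*

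**What the plan says.** All references are to the Protocol article.

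- **Outcome (Study outcome).** "Hypotension is defined as either a 30% reduction in mean arterial pressure (MAP) from baseline or absolute MAP ≤65 mm Hg". The scoring window opens at induction and closes at 15 minutes or at skin incision, whichever is earlier, with cuff readings every minute.
- **Baseline (Study outcome).** "Preoperative baseline blood pressure will be recorded when patients are comfortably seated in the ward".
- **Derivation (text under Figure 1, Data collection).** MAP is computed at each time point, and then "we will calculate the relative threshold (30% MAP reduction from baseline). Based on these, we can determine the occurrence of PIH".
- **Predictors.** The preoperative list has "Vital signs in the surgical ward including MAP and HR". The intraoperative list has "Vital signs including MAP and HR immediately before anaesthesia induction". The plan therefore collects both values needed to tell whether a patient meets the definition before induction.
- **Eligibility (Inclusion and Exclusion criteria).** The inclusion list covers age, ASA class, type of surgery and anaesthesia, and duration. The exclusion nearest to blood pressure is "Patients who have severe cardiovascular and cerebrovascular diseases, severe liver, kidney or lung dysfunction". The others concern regional anaesthesia, the airway ("Pre-existing tracheal intubation, tracheotomy or ≥2 attempts of intubations") and refusal. None refers to a blood pressure value.

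**The concern.** The model is meant to flag, ahead of time, hypotension that follows induction. That implies a population free of the event when prediction starts. Here the relative threshold is tied to a ward reading, while the state of the patient at the start of the risk period is captured by a different reading that plays no part in the outcome rule. A patient can be below threshold at that second reading, stay there for one minute after induction, and enter the data as a PIH event.

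For that patient the model predicts no response to anaesthesia. It recognises a state that two of its own inputs already describe. Such cases raise the PIH incidence, strengthen the apparent effect of pre-induction MAP and lift the AUC. The bootstrap and the temporal cohort use the same outcome rule, so neither would reveal it.

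**Working it through.** **1. Who is affected.** A patient meets the definition before induction if pre-induction MAP ≤ 65 or pre-induction MAP ≤ 0.70 × ward MAP. The relative limit is the higher of the two when ward MAP exceeds 65/0.70 = 92.9 mm Hg. With ward MAP 100 the limit is 70, so a pre-induction MAP of 69 qualifies. With ward MAP 110 the limit is 77. The group is therefore wider than patients at or below 65 mm Hg.

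**2. The plan's own figure.** Sample size estimation gives 23 × 10 / 0.35 = 657.1, which agrees with the stated 657. Expected development events are 657 × 0.35 ≈ 230, or 10 per candidate predictor. With the temporal cohort, 657 + 281 = 938.

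**3. Effect on the event count.** Let q be the share already below threshold. The documents do not give it, so 0.5% to 5% is assumed. If all of these patients are scored as PIH, 657q events are not new events. Events per variable (EPV) become (230 − 657q)/23, and the development sample needed to keep 230 new events is 230/(0.35 − q).

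| q | events not new | share of 230 | EPV | N needed |
|---|---|---|---|---|
| 0.5% | 3 | 1.4% | 9.9 | 667 |
| 1% | 7 | 2.9% | 9.7 | 676 |
| 2% | 13 | 5.7% | 9.4 | 697 |
| 5% | 33 | 14% | 8.6 | 767 |

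**4. How large q might be.** All blood pressure inputs here are assumptions.

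*Bivariate normal, ward MAP mean 97, SD 12:*
- Pre-induction mean 100, SD 14, correlation 0.5: 0.9% (about 8 of 938).
- Pre-induction mean 95, SD 14, correlation 0.5: 2.3% (about 22).
- Pre-induction mean 92, SD 15, correlation 0.4: 5.8% (about 54).
- Pre-induction mean 105, SD 14, correlation 0.5: 0.3% (about 3).

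*Second simulation.* Ward MAP is 95 (SD 11) or 90 (SD 12). The difference, pre-induction minus ward, has mean −5 to +10 and SD 8 to 14. The lowest MAP after induction is the pre-induction MAP less a random proportional fall, with the mean fall set to give 35% PIH. Selected settings:

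| ward MAP | mean difference (SD) | already below | share of PIH | AUC of pre-induction MAP alone, with → without them |
|---|---|---|---|---|
| 95 | +10 (8) | 0.15% | 0.4% | 0.689 → 0.688 |
| 95 | +5 (10) | 0.9% | 2.6% | 0.742 → 0.736 |
| 95 | 0 (14) | 5.0% | 14% | 0.824 → 0.796 |
| 90 | +5 (14) | 5.3% | 15% | 0.843 → 0.816 |
| 90 | −5 (14) | 14.5% | 40% | 0.885 → 0.818 |

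Across all settings, 96% to 100% of those already below threshold were scored as PIH, and the AUC of pre-induction MAP alone fell by 0.001 to 0.067 on removing them.

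**5. Effect on a model's AUC.** Assume AUC 0.70 and 35% PIH among patients at risk, and assume that those already below threshold rank at 0.97. With f their share of patients, their share of events is s = f/(0.35(1 − f) + f), and the apparent AUC is (1 − s) × 0.70 + s × 0.97.

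- f = 1%: s = 0.028, AUC 0.708.
- f = 2%: s = 0.055, AUC 0.715.
- f = 3%: s = 0.081, AUC 0.722.

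For comparison, the Hanley-McNeil standard error at AUC 0.70 and 35% events is about 0.034 with 281 patients and 0.022 with 657.

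**The case against.** A reader might infer that pre-induction MAP predicts the outcome by definition, or that it fixes the outcome. The text does not support that. Only readings after induction are scored, so a patient who starts below threshold becomes a case only if a later, separate reading also qualifies. That is near-certain, but it is an empirical matter and is confined to this subgroup. For everyone else pre-induction MAP is an ordinary prognostic variable, measured before the outcome, and most of its discrimination remains once the subgroup is removed.

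The group may also be very small. The Discussion justifies the ward baseline by anxiety on entering the operating room, which suggests that awake pressure there is at or above ward pressure. Patients are elective, ASA I to III, without severe cardiovascular disease. In the low scenarios the AUC shift is well inside one standard error. This lowers the priority. It does not remove the point, because the shift is systematic and has the same direction in both cohorts. The anxiety argument does not guarantee a small group either: with pre-induction MAP averaging 5 to 10 mm Hg above ward MAP, the second simulation still gives 0.15% to 5.3% of patients.

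Keeping everyone who reaches induction could be defended as the target population of a universal model. That is a coherent choice, but the article does not state it, and it sits poorly with the aim of identifying post-induction events in advance. The flowchart and case report form are not shown and could contain a check before induction. The criteria and the outcome rule that the article does set out contain none.

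**Conclusion.** The concern holds in limited form. As written, the outcome rule and the eligibility criteria let hypotension that was present before induction, and persists, count as PIH in both the development and the temporal validation cohort. The effect is some inflation of incidence and apparent discrimination. No stated figure is wrong, and no two passages contradict each other.

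The size cannot be derived from the documents. It depends on the assumed means, spread and correlation of ward and pre-induction MAP. It may be under 1% of patients with an AUC change below 0.01, most plausibly if operating-room pressure is at or above ward pressure. It may be several percent if pressure falls between the two readings or varies widely within patients. The highest simulated share, 14.5%, comes from the most unfavourable inputs and should not be read as an estimate. The point is worth correcting because the correction is cheap and because only the count of such patients can settle how much it matters.

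**What to change.** Derive one flag from the two values already recorded: pre-induction MAP ≤ 65 mm Hg, or pre-induction MAP at least 30% below ward MAP. Then:

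1. Leave flagged patients out of the at-risk analysis set for model development, bootstrap validation and temporal validation. At minimum, repeat the model and its validation without them.
2. Report the number flagged in each cohort, and how many of them were scored as PIH.
3. State the same restriction on the nomogram and web calculator. Both values are known before induction, so the restriction can be applied at the time of use.

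This is a rule for the analysis set and changes nothing in patient care. It costs a sentence in the methods and a derived variable. The downside is the loss of a small number of patients and events, with slightly lower EPV and AUC. At a 1% share EPV falls from 10 to 9.7, and keeping 230 new events would need about 676 development patients in place of 657.
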